## Abstract

**Background:** SARS-CoV-2 infection affects the vascular endothelium, which mediates the inflammatory and thrombotic cascade. Moreover, alterations in the endothelium are related to arterial stiffness, which has been established as a marker of cardiovascular disease. The objective of this study is to analyse how the structure, vascular function, vascular ageing and endothelial damage are related to the biopsychological situation in adults diagnosed with persistent COVID and the differences by gender.

**Methods:** This cross-sectional, descriptive, observational study will be carried out in the Primary Care Research Unit of Salamanca (APISAL) and in the BioSepsis laboratory of the University of Salamanca. The sample will be selected from the persistent COVID monographic office at the Internal Medicine Service of the University Hospital of Salamanca, and from the population of subjects diagnosed with persistent COVID in the clinical history of Primary Care. Through consecutive sampling, the study will include 300 individuals diagnosed with persistent COVID who meet the diagnosis criteria established by the WHO, after they sign the informed consent. Endothelial damage biomarkers will be measured using ELLA-SimplePlexTM technology (Biotechne). Their vascular structure and function will be analysed by measuring the carotid intima-media thickness (Sonosite Micromax); the pulse wave and carotid-femoral pulse wave velocity (cfPWV) will be recorded with Sphygmocor System^®^. Cardio Ankle Vascular Index (CAVI), brachial-ankle pulse wave velocity (baPWV) and ankle-brachial index will be analysed with Vasera VS-2000^®^. The integral assessment of the subjects with persistent COVID will be conducted with different scales that evaluate fatigue, sleep, dyspnea, quality of life, attention, nutrition state, and fragility. We will also evaluate their lifestyles (diet, physical activity, smoking habits and alcohol consumption), psychological factors, and cognitive deterioration, which will be gathered through validated questionnaires; moreover, physical activity will be objectively measured using a pedometer for 7 days. Body composition will be measured through impedance using an Inbody 230. Vascular ageing will be calculated with 10 and 90 percentiles of cfPWV and baPWV. Furthermore, we will analyse the presence of vascular injury in the retina, heart, kidneys and brain, as well as cardiovascular risk. Demographic and analytical variables will also be gathered.

**Discussion:** Arterial stiffness reflects the mechanic and functional properties of the arterial wall, showing the changes in arterial pressure, blood flow, and vascular diameter that occur with each heartbeat. SARS-CoV-2 affects the endothelial cells that are infected with this virus, increasing the production of pro-inflammatory cytokines and pro-thrombotic factors, which can cause early vascular ageing and an increase of arterial stiffness. Persistent COVID is a complex heterogeneous disorder that affects the lives of millions of people worldwide. The identifications of potential risk factors to better understand who is at risk of developing persistent COVID is important, since this would enable early and appropriate clinical support. It is unknown whether vascular alterations caused by COVID-19 resolve after acute infection or remain over time, favouring the increase of arterial stiffness and early vascular ageing. Therefore, it is necessary to propose studies that analyse the evolution of persistent COVID in this group of patients, as well as the possible variables that influence it.

**Clinical Trial registration:**
ClinicalTrials.gov, identifier NCT05819840

## 1 Introduction

SARS-CoV-2 infection (COVID-19) affects multiple organs and systems, with a large number of clinical manifestations described in the literature (Luo et al., 2022), causing endothelium injuries, local microthrombotic events and an inflammatory state (Lazzaroni et al., 2021; Clemente-Suárez et al., 2022; Gusev et al., 2022; Sbirkov et al., 2022). The severity of this disease is influenced by age and the presence of cardiovascular risk factors such as hypertension, type-2 diabetes mellitus and obesity, which is probably related to vascular alterations that lead to the former two (Harrison et al., 2021), and the association of low-grade inflammation with obesity (Chiappetta et al., 2020). SARS-CoV-2 can infect endothelial cells through the angiotensin converting enzyme 2 (ACE2), downregulating the expression of this enzyme, consequently losing its protective effects, and thus favouring vascular inflammation and the increase of arterial stiffness and organic injury (Monteil et al., 2020; Gnanenthiran et al., 2022).

At the end of spring 2020, when the efforts began to be implemented to control the first wave of cases, it was observed that, in some patients affected by COVID-19, the symptoms persisted weeks after overcoming the acute phase. All this has been subsequently confirmed, observing that, after acute infection, a considerable percentage of individuals continued to present symptoms. This has generated a situation of uncertainty, for both patients and healthcare professionals, since there were neither certainties nor tools to establish a precise diagnosis, as the latter depends, in most cases, on the testimony of the patient about his/her symptoms and, most importantly, on the impact of the symptoms on his/her functioning and quality of life (Abrignani et al., 2022; Raman et al., 2022). Numerous terms have been used to refer to this new entity (Chaichana et al., 2023); the most accepted terms are persistent COVID and long COVID (Lopez-Leon et al., 2021; Mandal et al., 2021; Abrignani et al., 2022; Sugiyama et al., 2022), and a large number of organisations have attempted to provide a validated definition that is accepted by the scientific community. The multiple definitions that have emerged, since the appearance of the first cases, consider it as a multi-organ disease that affects those patients that have suffered from COVID-19, with persistent symptoms and fluctuating frequency, and without an alternative underlying illness that can explain such symptoms (Abrignani et al., 2022; Rubin, 2020; SemFYC: Manifestaciones Persistentes de la Covid-19, 2020; Siegelman, 2020; Severe Acute Respiratory Syndrome, 2021; Shah et al., 2021; Yang et al., 2021; Rodriguez-Sanchez et al., 2022; Centers for Disease Control, 2022; Rodriguez Ledo, 2021).

Currently, the most accepted definition is the one agreed upon by the WHO; this organisation considers persistent COVID as the post-COVID affectation that occurs in individuals with a history of probable or confirmed infection by SARS-CoV-2, which generally continues three months after the appearance of COVID-19 with symptoms that last for at least two months and which cannot be explained by an alternative diagnosis. The most common symptoms are fatigue, difficulty in breathing, and cognitive dysfunction, although other symptoms that usually affect the quality of life can also occur. The symptoms can be de novo, after the initial recovery from an acute episode of COVID-19, or they may persist from the beginning of the disease. They can also fluctuate or there may be relapses over time (Soriano et al., 2022).

Due to the clinical variability and the lack of a shared and specific definition, as well as to the different data gathered, it is very difficult to know the actual prevalence and rate of persistent COVID, which is demonstrated by the great variation among studies (Abrignani et al., 2022; Sugiyama et al., 2022). Systematic reviews and meta-analyses also report great variability in the prevalence of persistent COVID-19, ranging between 30% and 80% of people infected (Lopez-Leon et al., 2021; Chan Sui Ko et al., 2022; Wulf Hanson et al., 2022). Similarly, the cohorts of patients have described different prevalences. Thus, Hossain et al. 2021, at 31 weeks of follow-up, found that the prevalence of prolonged symptoms of COVID was 16.1%. Another study conducted in the Netherlands revealed that one out of eight adults (12.7%) infected by COVID-19 experienced long-term symptoms (Ballering et al., 2022). The United States National Center for Health Statistics reported that one out of five adults who had suffered from COVID-19 was experiencing persistent COVID (Centers for Disease Control and Prevention, 2022). In Spain, it is estimated that at least 10% of people infected present symptoms that can be attributed to this affectation. (Rodriguez Ledo, 2021) Therefore, assuming the most favourable prevalences, persistent COVID still affects millions of people in the world.

Currently, the following are recognised as risk factors of persistent COVID: being a middle-aged woman (Abrignani et al., 2022; Bai et al., 2022; Tsampasian et al., 2023), having been hospitalised for severe symptoms of COVID-19 during the acute phase (Iqbal et al., 2021) and having a worse initial state of health or previous medical comorbidities (Tsampasian et al., 2023), such as depression (Knight et al., 2022), smoking (Hossain et al., 2021), dyslipidemia (Loosen et al., 2022), previous chronic bronchopathy (Loosen et al., 2022), arterial hypertension (Chan Sui Ko et al., 2022; Loosen et al., 2022), diabetes mellitus (Steenblock et al., 2022), autoimmune diseases (Abrignani et al., 2022) and obesity (Abrignani et al., 2022; Loosen et al., 2022). Lower prevalence is reported in people vaccinated against COVID-19 (Azzolini et al., 2022; Tsampasian et al., 2023), showing an inverse relationship with the number of doses received (Azzolini et al., 2022; Kuodi et al., 2022). However, most people with on-going persistent COVID have not experienced changes in their symptoms after vaccination (Watanabe et al., 2023). In the prospective cohort study of Salud de Enfermeras (Nurses’ Health), six healthy lifestyles were considered before the infection, observing that the larger the number of healthy lifestyles prior to the infection, the lower the risk of persistent COVID after the acute infection (Wang et al., 2023).

Persistent COVID is a multi-systemic affectation, presenting in a wide variety of manifestations, where up to 203 symptoms have been identified (Abrignani et al., 2022), including fatigue, post-effort discomfort, dyspnea, chest pain, cognitive deterioration, sleep disorders, anxiety and depression, muscle pain, brain fog, difficulty in concentrating, mental confusion, anosmia/dysgeusia, headache with limitation of the functional capacity, and deterioration of the quality of life (Stein et al., 2022; Romero-Rodríguez et al., 2023; Zeng et al., 2023). According to a recent meta-analysis, people with persistent COVID show a decrease of the initial symptoms (from 92% in the acute phase to 55% at one month of follow-up), followed by stabilisation of approximately 50% for one year. Six or more months after the acute phase, the odds ratio of factors related to the characteristics of the population increased (from 1.62 to 1.82 in women), whereas the value of the odds ratio of the factors related to the acute phase (severe or critical cases and hospitalisation) decreased, and the neuropsychiatric symptoms showed greater prevalence in the long term (approximately 25%) and longer persistence than the physical symptoms (Alkodaymi et al., 2022). Likewise, the psychological consequences of the disease caused by persistent COVID have been reported in different studies (Mandal et al., 2021; Sher, 2021), although the conclusions are not clear, and thus further research is necessary in this respect (Sher, 2021). One of the main characteristics of the disease caused by persistent COVID is the predominance of neurocognitive affectation, which is specifically manifested through problems of attention and memory (78.2% and 72.6% of cases in Spain, respectively) (Rodriguez Ledo, 2021). A relevant number of subjects who have suffered from COVID-19 present post-traumatic stress syndrome, anxiety, depression and insomnia (Mazza et al., 2020). A previous study has related post-traumatic stress syndrome with arterial stiffness (AS) (Tomlinson and Cockcroft, 2011). Moreover, patients with persistent COVID present high levels of inflammatory biomarkers after the initial infection (Lai et al., 2023), and other studies show a dissociation between the symptoms and the objective findings, using standard diagnostic tests (Zota et al., 2022).

The alteration in the structure of the vascular wall evaluated with carotid artery ultrasound and ankle-brachial index (ABI) along with AS have been used as biomarkers to improve the prediction of cardiovascular risk (Visseren et al., 2021). AS presents with a decrease of artery elasticity, and it is a predictor of risk of cardiovascular diseases of similar or greater importance with respect to other traditional cardiovascular risk factors (Visseren et al., 2021). Thus, AS measured in a non-invasive manner, with carotid femoral pulse wave velocity (cfPWV), brachial-ankle pulse wave velocity (baPWV), and cardio-ankle vascular index (CAVI), has shown a positive association with cardiovascular events (Ohkuma et al., 2017; Zhong et al., 2018; Matsushita et al., 2019; Miyoshi et al., 2021; Yasuharu et al., 2021). AS is mainly determined by age, sex and arterial pressure (Laurent et al., 2019; Visseren et al., 2021). In this way, when the central arteries become more rigid, they maintain their duct functions, although they progressively lose their storage properties (Williams et al., 2018a). AS is related to cardiovascular risk factors, lifestyles, inflammatory factors, and psychological factors (Avolio, 2013; Tsai and Hsu, 2021). Therefore, its detection can play an important role in the prevention of cardiovascular diseases, as its alteration appears before the vascular structure is affected (Williams et al., 2018a). Currently, we can measure vascular structure and function in a non-invasive manner. cfPWV, measured with tonometry, is considered the measure of reference (Williams et al., 2018a). cfPWV depends on the arterial pressure at the time of the measurement, and it reflects the AS of the descending aorta, iliac arteries, the first portion of the femoral arteries, the brachiocephalic trunk, and the common carotid artery, without evaluating the ascending aorta, and it is a measure of central AS (Boutouyrie and Vermeersch, 2010). baPWV, measured by oscillometry, is a measure of peripheral AS (Munakata, 2016). CAVI, also evaluated through oscillometry, analyses the stiffness of the aorta (including the ascending aorta) and the iliac, femoral and tibial arteries; it does not depend on the arterial pressure at the time of the measurement, and it is considered a measure of both central and peripheral AS (Shirai et al., 2011; Namba et al., 2019). AS is associated with the appearance of vascular ageing (Nowak et al., 2018; Laurent et al., 2019), reflecting the dissociation between the chronological and biological age of the major arteries, with their alteration preceding the appearance of cardiovascular events (Williams et al., 2018a; Nowak et al., 2018; Laurent et al., 2019). Vascular ageing is used for the early identification of subjects that could benefit from primary prevention. It is described as a gradual process that involves biochemical, enzymatic and cellular processes in the vascular area combined with epigenetic and molecular alterations, and it is considered that it is a fundamental reflection of biological ageing in general, and a determinant of vascular functioning (Mikael et al., 2017; Nowak et al., 2018). During the last decades, epidemiological studies have been conducted to unravel the determining factors of vascular ageing, drawing great interest, as it shows a stronger relationship with morbimortality by cardiovascular diseases than biological ageing (Nowak et al., 2018; Laurent et al., 2019). In this sense, it is known that early vascular ageing (EVA), normal vascular ageing (NVA) and healthy vascular ageing (HVA) are related to the progression of the deleterious characteristics of arterial functioning, which is influenced by the genetic background, the prevalence of classic cardiovascular risk factors, lifestyles and inflammatory factors (Niiranen et al., 2017; Botto et al., 2018; Ji et al., 2018; Nilsson et al., 2018; Nowak et al., 2018; Foscolou et al., 2019). The effect of physical activity on vascular ageing has been analysed in numerous studies, confirming that it plays an important role by mitigating vascular ageing, increasing the availability of nitric oxide (NO) and reducing oxidative stress and vascular wall inflammation (Andersson et al., 2015; Antunes et al., 2016; Jakovljevic, 2018; Zhang et al., 2018; Kucharska-Newton et al., 2019; Gomez-Sanchez et al., 2020). However, some authors suggest that this effect is different between sexes (Seals et al., 2019) and varies depending on the type of physical activity performed (Li et al., 2015). The benefits of the Mediterranean diet (Martinez-Gonzalez et al., 2019; Papadaki et al., 2020; Liu et al., 2021; Morze et al., 2021) and the influence of smoking habits and alcohol consumption on cardiovascular diseases (Kondo et al., 2019; Gonzalez-Sanchez et al., 2020) is widely demonstrated. Lastly, the psychological factors can worsen the inflammatory response or increase the blood levels of cortisol (Shah et al., 2011). Thus, different psychological components such as anxiety, depression and chronic stress can enhance vascular ageing. Nevertheless, the relationship among the determining factors of vascular ageing continues to be an area of interest for research (Gomez-Sanchez et al., 2022). Therefore, maintaining a process of NVA is fundamental for preserving vascular health and delaying the appearance of cardiovascular diseases (Mikael et al., 2017; Nowak et al., 2018). Currently, there is no consensus on a definition of vascular ageing. In this regard, several authors have defined HVA, excluding hypertensive or diabetic subjects from the group of HVA (Niiranen et al., 2017; Ji et al., 2018; Nilsson et al., 2018), and using the percentiles of cfPWV below 10 or 25 from a reference population, or from their own study population, stratified by age groups, and some authors also take into account the values of arterial pressure. Different definitions of EVA have also been published (Van Bortel et al., 2012; Cunha et al., 2015; Cunha et al., 2017; Botto et al., 2018), which are gathered in several studies that consider the highest percentiles of cfPWV for its definition. Various works have employed the values published by Boutouyrie et al. in a European population as reference values (Boutouyrie and Vermeersch, 2010). Our research group has recently published reference values of the different measures of AS for the Spanish adult population without previous cardiovascular disease (Gómez-Sánchez et al., 2020a). Furthermore, we have analysed AS in a general population without cardiovascular disease, measured with several parameters and using different criteria of vascular ageing, analysing their relationship with lifestyles, cardiovascular risk factors, inflammatory factors and psychological factors (Gómez-Sánchez et al., 2020b; Gomez-Sanchez et al., 2020; GómezSánchez et al., 2020). Therefore, we consider that the best definition of vascular ageing must be that which considers the following variables: age, arterial pressure and sex (i.e., the variables with greatest influence on AS), as well as the percentiles of cfPWV of the study population.

During the COVID-19 pandemic, some studies have evaluated the impact of SARS-CoV-2 infection on AS, showing greater AS among the deceased and subjects who presented longer hospitalisation, which may guide toward the prognostic value of such parameter (Schnaubelt et al., 2021). Another study, conducted in a young population, reported lower vascular function and greater AS in the group affected by SARS-CoV-2 at 3-4 weeks, calculated through reactive hyperemia and cfPWV (Ratchford et al., 2021). In this sense, pulse pressure ≥ 60 mmHg upon admission, as a substitute marker of AS, has been associated with an increase of mortality by all causes (Rodilla et al., 2021). A study performed in India, in three groups of patients with acute SARS-CoV-2 infection stratified according to severity, found an association between severity and AS measured with cfPWV; moreover, in seriously ill patients, AS induced by SARS-CoV-2 infection was greater than that reported in control patients with a high load of cardiovascular risk factors (Kumar et al., 2021). Lastly, it has been observed that the data of vascular ageing induced by COVID-19 improve over time, although such parameters of vascular ageing continue to be altered with respect to the reference values obtained in the measurement conducted at 12 months of infection (Zanoli et al., 2022). AS is also associated with the severity and duration of systemic inflammation and low-grade inflammation (Zanoli et al., 2020). SARS-CoV-2 infection presents with multisystemic inflammation and an altered immune response, which could cause deleterious effects on the blood vessels in the short and long term; in turn, this is associated with the severity of the disease and the persistence of symptoms (Zanoli et al., 2017; Dan et al., 2021), which suggests that it can be the connecting link between AS, vascular ageing and persistent COVID. Although the underlying biological mechanisms are still unknown, an abnormal or excessive autoimmune and inflammatory response can play an important role (Carod-Artal, 2021). Furthermore, these late inflammatory, immunometabolic changes produced by SARS-CoV-2 infection and the unresolved defects of immune cells, if maintained, may contribute to the persistence of the symptoms and the development of persistent COVID (Carod-Artal, 2021). Therefore, markers of endothelial damage may play an important role in the development of long COVID, and one of the hypotheses is that the existence of post-COVID endotheliopathy, predominantly microvascular with accompanying low-grade inflammation, could be behind most of the symptoms of this disease (Fogarty et al., 2021; Ahamed and Laurence, 2022). One of the non-invasive methods for studying endothelial function is the quantification of endothelial biomarkers and inflammatory mediators in plasma, the levels of which increase when the endothelium is activated or damaged, allowing valuable information to be obtained both on the status of the endothelium and on the immunological state of the patient. Previous studies have identified biomarkers of a dysregulated response to SARS-CoV-2 infection (Bermejo-Martin et al., 2020). These biomarkers include endothelial function molecules (ICAM-1, VCAM-1, Angiopoietin-2, Endothelin-1), inflammation (IL-6, IL-15, TNF-alpha), immunosuppression (IL-10, PD- L1), virus control/chemotaxis (CXCL10) and interferon response (IFN-gamma). They all participate in key physiological pathways in the pathogenesis of acute COVID-19 and could remain impaired in patients with long COVID. Their quantification in plasma could provide relevant information on the mechanisms of endothelial pathology and immunological dysfunction in these patients, which could improve the diagnosis, monitoring and treatment of this disease.

To sum up, persistent COVID may affect the entire spectrum of COVID-19 patients, from those with a very mild acute disease to those who are seriously ill. The symptoms are heterogeneous, including fatigue, post-effort discomfort, dyspnea, cognitive deterioration, sleep disorders, anxiety and depression, muscle pain, brain fog, anosmia/dysgeusia, headache and limitation of the functional capacity, which affect the quality of life of the patients. The relationship between AS and vascular ageing is not clear. The starting hypothesis of this study states that individuals diagnosed with persistent COVID present greater alteration in the vascular structure and function, as well as worse vascular ageing, compared to the general population without a diagnosis of persistent COVID, since the vascular system of these people is subjected to complex inflammatory deregulation, which has not been studied to date.

Therefore, the main objectives of this study are: 1) to analyse vascular structure, vascular function, biomarkers of endothelial damage and ageing in Spanish adults diagnosed with persistent COVID, determining the differences between sexes; and 2) to analyse the association of the clinical symptoms, lifestyles (physical activity, diet, alcohol consumption and smoking habits), and psychological, cognitive and inflammatory factors with biomarkers of endothelial damage, vascular structure, function and ageing, determining the differences by sexes. Regarding the secondary objectives of this study, we will analyse the possible differences among individuals with persistent COVID according to whether the infection is caused by the Delta mutation or the Omicron mutation. Furthermore, in order to continue advancing in the recognition and visibility of the patients affected by persistent COVID, they will be given a voice through a focal discussion group, where we will delve into the opinions and experiences of the population to facilitate the transfer of the study to the habitual clinical practice.

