## 2 Methods and analysis

### 2.1 Study design and context

This will be a cross-sectional, descriptive, observational study in which we will analyse vascular structure, function and ageing and biomarkers of endothelial damage, and their relationship with lifestyles and psychological and inflammatory factors in adults with persistent COVID. The discussion groups will investigate the opinions and experiences of what the affectation by persistent COVID posed to these patients. The Persistent COVID study (GRS 2501/B/22) was registered in ClinicalTrials.gov (registration number: NCT05819840) in April 2023. In order to know if the subjects with persistent Covid have the parameters of structure, of vascular function, as well as the degree of altered vascular aging, we will use as a reference group, the values of these parameters available in the results of the EVA Study in the general population without previous cardiovascular disease (Gómez-Sánchez et al., 2020a), and we will also compare the results with other reference populations (Determinants of pulse wave velocity, 2010; Engelen et al., 2013; Herbert et al., 2014; Cunha et al., 2015). The study will be developed in the Primary Care Research Unit of Salamanca (APISAL) during the year 2023. In this period, we will select the sample and gather the data through questionnaires and explorations, which are described below. This project was approved by the ‘Ethics Committee of Research with Medicines of the health area of Salamanca’ on 27/06/2022 (CEIm reference code: Ref. PI 2022 06 1048). The SPIRIT verification list (Standard Protocol Items: Recommendations for Interventional Trials) (Chan et al., 2013) is available for this protocol (Supplementary Material S1).

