#### 2.3.7 Vascular ageing

Vascular ageing will be evaluated with cfPWV, baPWV or vascular age estimated using a VaSera VS-2000 device (Fukuda Denshi Co, Ltd, Tokyo, Japan) as measures of arterial stiffness. Firstly, the subjects who present vascular injury (injury in the carotid artery or peripheral arteriopathy) will be classified as EVA. Secondly, the subjects will be classified as EVA, NVA and HVA if the values of cfPWV or baPWV are above percentile p90, between p10 and p90, and below p10, respectively. (Gomez-Sanchez et al., 2020)

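### The protocol conflicts on whose percentiles define vascular ageing; if the patients' own are used, the percentile step cannot show that they are stiffer than the general population

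*Protocol article*

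**What the plan says.** The starting hypothesis in section 1 includes "worse vascular ageing, compared to the general population without a diagnosis of persistent COVID". Three places bear on how vascular ageing is graded.

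- **Section 1 (Introduction).** The authors describe earlier definitions as "using the percentiles of cfPWV below 10 or 25 from a reference population, or from their own study population, stratified by age groups", so they know that the two sources differ. They end by preferring a definition that considers age, arterial pressure and sex, "as well as the percentiles of cfPWV of the study population".
- **Section 2.1 (Study design and context).** To learn whether structure, function and the degree of vascular ageing are altered, "we will use as a reference group, the values of these parameters available in the results of the EVA Study". Other published reference populations will also be compared.
- **Section 2.3.7 (Vascular ageing).** First, "the subjects who present vascular injury (injury in the carotid artery or peripheral arteriopathy) will be classified as EVA". Then "the subjects will be classified as EVA, NVA and HVA if the values of cfPWV or baPWV are above percentile p90", with normal vascular ageing (NVA) and HVA taking the other two bands: "above percentile p90, between p10 and p90, and below p10, respectively". No source population and no age or sex strata are given. The section also lists a device-estimated vascular age, without a class rule for it.

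The Abstract does not settle the question: "Vascular ageing will be calculated with 10 and 90 percentiles of cfPWV and baPWV".

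**The concern.** The study enrols patients only. If p10 and p90 are computed from those patients, the cut-offs move with them. A cohort with normal arteries and a cohort one standard deviation stiffer would then show the same percentile-based shares. The classification would have lost its comparator, although the hypothesis is about a comparison with the general population.

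The ambiguity is more than a detail left to another document. The only sentence that says whose percentiles should define the classes points to the study population, while the section that names the comparator for vascular ageing points outside it. An analyst who follows the first could report no excess of early vascular ageing when the design difference is truly present.

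Main objective 1 also asks for differences between the sexes. The Introduction's preferred definition considers sex. If that were implemented as separate own-sample cut-offs for men and women, the percentile-based sex comparison would be levelled as well.

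**Working it through.** **Inputs.** From section 2.2: difference in cfPWV of 0.35 m/s from a Spanish population without cardiovascular disease, SD 2.1 m/s, two-sided alpha 0.05, beta below 0.2, 283 required and 300 planned. From section 2.3.7: cut-offs p10 and p90, lesion step first, cfPWV or baPWV. Assumptions: normality; for the simulation, a correlation of 0.5 to 0.7 between cfPWV and baPWV and a lesion prevalence of 0 to 20%.

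**The plan's own figure.** For one mean against a fixed reference value, n = (SD × (1.960 + 0.842) / difference)² = (2.1 × 2.8016 / 0.35)² = 282.56, rounded up to 283. This matches exactly. Power at 300 is 82.3%. The sample size therefore already rests on an external reference for mean cfPWV.

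**Reference cut-offs.** Let s = shift / SD. The share above the reference p90 is 1 − Φ(1.2816 − s), and the share below the reference p10 is Φ(−1.2816 − s).

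| True shift | s | EVA, reference | HVA, reference | EVA / HVA, own sample |
|---|---|---|---|---|
| 0 | 0 | 10.0% | 10.0% | 10% / 10% |
| 0.35 m/s | 0.167 | 13.2% | 7.4% | 10% / 10% |
| 2.1 m/s | 1 | 38.9% | 1.1% | 10% / 10% |

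The last column is cfPWV alone, before any lesion step. The 2.1 m/s row is illustrative; it is six times the design difference.

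**Full two-step rule with own-sample cut-offs** (simulation, 300 patients, 500 runs per setting, shifts of 0, 0.167 and 1 SD):

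- Either-measure rule, no lesions: about 15–17% in each tail.
- cfPWV alone, lesion prevalence 5–20%: EVA about 14–28%, HVA about 8–9.5%.
- Either-measure rule, lesion prevalence 5–20%: EVA about 20–34%, HVA about 12–16%.

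These totals move with lesion prevalence and with the assumed correlation. They do not move with the stiffness shift beyond simulation noise. For example, with correlation 0.5 and 10% lesions, the either-measure EVA share is 25.2%, 25.2% and 25.1% at the three shifts.

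**Sex.** As an illustration not taken from the documents, suppose women are shifted by 0.7 m/s and men by 0. Then s = 0.7 / 2.1 = 0.333, and reference cut-offs give 1 − Φ(0.948) = 17.2% EVA in women against 10.0% in men. Sex-specific own-sample cut-offs give 10% and 10%. Pooled own-sample cut-offs would still separate the sexes.

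**Precision of the corrected comparison.** Testing 13.2% against a fixed 10% with 300 patients has a power of about 47%, against 82.3% for the mean. The class shares are thus a weaker reading of the same shift even when the cut-offs are right.

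**The case against.** The strongest reply is that the Introduction sentence is an opinion at the end of a literature review, and that section 2.3.7 does not restate it. The sentence follows remarks on the group's Spanish reference values and its work in a general population, so the study population in it might mean that earlier cohort. Section 2.1 is the only Methods text on the comparator for vascular ageing, and it names the EVA Study. This stands so far as it goes: the documents do not show that own-sample percentiles will be used. It does not remove the conflict, because 2.3.7 is silent and the one sentence on the point favours the other source.

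Three stronger readings are tempting, and the documents do not support them.

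- A reader might infer that 10% of patients will be early and 10% healthy by construction. That describes only the cfPWV percentile step. The lesion-first step and the choice of either measure shift the totals.
- A reader might infer that the hypothesis cannot be tested. Mean cfPWV against the Spanish reference drives the sample size, section 2.4 plans Z scores for comparison with reference populations, and device vascular age and lesion prevalence are also available. However, cfPWV is listed under vascular function, and the hypothesis names vascular ageing separately, so those analyses do not repair the classification itself.
- A reader might infer that the sex objective has a predetermined answer. That holds only for sex-specific own-sample cut-offs, which 2.3.7 does not state.

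Relative classes are also legitimate for the within-sample associations of main objective 2.

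**Conclusion.** The point holds as an internal conflict between section 1, section 2.1 and section 2.3.7, with a conditional consequence. If the patients' own percentiles are used, the percentile step cannot respond to a stiffness shift. At the protocol's own design difference, the loss on cfPWV is 13.2% EVA and 7.4% HVA reported as 10% and 10%. In that case the classification cannot show, through stiffness, worse vascular ageing than the general population. With sex-specific own-sample cut-offs it cannot show a sex difference either.

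The figures rest on normality and on one SD of 2.1 m/s in patients and reference alike. If the SD within age and sex strata is smaller, the same 0.35 m/s is a larger shift in SD units and the lost contrast is greater. The simulated totals rest on assumed correlations and lesion prevalences, but their insensitivity to the shift does not. Which source the authors intend cannot be settled from the document.

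**What to change.** 1. In 2.3.7, state that p10 and p90 for the general-population comparison are the published EVA Study reference percentiles, by age and sex, applied unchanged to the patients. The protocol says that reference values are published but does not say how they are stratified, so the strata should be confirmed and named.
2. Align the closing sentence on the definition of vascular ageing in section 1.
3. Keep own-sample percentiles, if at all, only for within-sample associations, and label them so.
4. In 2.4, state that the Z scores use the reference mean and SD.
5. Compare the percentile-step shares with the reference 10% and 10%, for cfPWV and baPWV separately and in all patients before the lesion step. Under the either-measure rule the no-effect share is not 10%.
6. Report lesion-based EVA separately, unless individual EVA Study data allow the same two-step rule to be applied there. The protocol promises reference values from that study's results, not individual carotid and peripheral-artery data.

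The cost is wording and a little analysis work, with no extra patient measurement. Applying the two-step rule to the reference would add a data request, which is why it is optional.
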